## **c. Data Analysis Objectives 1-5**

Our general analytic plan will be the same for each of Cohorts 1-5. We will begin with descriptive analyses of the characteristics of each of the cohorts stratified by intervention/non-intervention (comparison) cohorts. We will also look for differences within the randomized matched pairs. Because the data will be collected as part of a clustered design, the data analysis will need to account for clustering. For each primary outcome described above, we will conduct a crude analysis comparing the proportion of subjects with the outcome in the intervention and comparison arms. Next we will conduct an analysis for each outcome accounting only for clustering using generalized estimating equations (GEE) with an unstructured correlation matrix and clustering by treatment site. In all cases the outcomes are dichotomous and therefore we will calculate relative risks comparing the intervention to the comparison arms using a log link function and a binomial distribution. Next, should any imbalances between treatment groups be detected, we will adjust for those covariates in our GEE model. Finally, we will look for differences in the effects of the strategies by important baseline characteristics (e.g. size of the treatment population, rural vs. urban, province, etc.) using stratified analyses.

We note that because each of the interventions is targeted at a different population with the exception of decentralized medication delivery and adherence clubs, which would not be delivered to the same people at the same time, we can estimate the impact of each intervention separately, as only one of them will be delivered to each cohort within a clinic at any one time. Since some patients may participate in more than one intervention (e.g. fast track initiation followed by tracing), we will conduct a sub-analysis restricted to those who received only one intervention to look for the effects of each intervention by itself.

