# EVALUATION OF INTERVENTION EFFECTIVENESS (OBJECTIVES 1-5)

To achieve the first five objectives, we will test the effectiveness of five interventions included in the minimum package of adherence interventions using routinely collected data only. The interventions have been developed by the NDOH and will be implemented by the public sector clinics using their own staff and resources. Those interventions included in the evaluation were selected as having outcomes that could be assessed in a relatively short period of time, so that results can be used to refine the national guidelines and implementation. Below we detail each of the interventions and the populations we will use to evaluate the interventions.

We will use a matched cluster randomized design to evaluate the impact of each of the selected interventions. The National Department of Health, in consultation with the study team, will develop a short list of candidate primary health care clinics where early implementation of the package can occur. This short list will include proposed matched pairs of facilities which will be randomized to either implement the minimum package or not. Clinics will be matched on characteristics that are likely to affect study outcomes (patient volume, urban/rural location, current HIV viral suppression rate).

Because the interventions will be implemented clinic-wide and the evaluation will rely on routinely collected data only, we will include the entire patient population at each study site. All non-pregnant adult patients seeking HIV-related services at the study sites and eligible to receive one of the adherence interventions during the enrollment period will be included in the study through use of their clinic data. There will be no direct interaction with study subjects. Data will be collected from existing, routinely completed patient records, including clinic files, registers, cards, and databases. No additional data fields, beyond what are currently mandated under government guidelines, will be collected for the study. We assume that all study sites will follow the current guidelines for HIV care and treatment, dated December 2014[10] and the Primary Care 101 guide for TB, HIV, diabetes and hypertension care and treatment, dated 2013/14[15] as well as comply with the National Health Act of 2003.

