- *Setting*. Both sites in each pair should draw from the same type of community: urban; informal settlement; or rural.
- *Location*. Pairs should be located relatively nearby one another, to facilitate data collection and increase similarity of the catchment populations.

- *HIV viral suppression*. The clinics in the pair should have ART patient viral suppression rates within 10% percent of one another (if data available).

Letters indicating Provincial and District Department of Health authorization to work at each study site have been obtained and are attached. The final number of clinics selected remains at 24 clusters.

In each pair, one clinic will randomly be assigned to receive early implementation of the minimum package of interventions, while the other will continue to provide standard of care. Randomization will be done through a random number generator in Microsoft Excel with a 1:1 ratio of allocation to intervention and control clusters.

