## **b. Sample Size**

Table 4 shows the sample size that is required to detect meaningful differences for Objectives 1-5 and for estimating precise rates for Objective 8. Each sample size is determined to measure our short term outcome for the objective. For Objectives 1-5, all calculations assume a site-clustered design with the clinic as the cluster; 24 clusters evenly split (randomized) between intervention and comparison groups; a coefficient of variation of 0.1, 80% power; and an alpha of 0.05.

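### The unstructured GEE planned for Objectives 1-5 asks 24 clinics for 276 to 861 correlations and cannot be estimated as written; it also leaves out the matched pairs, which mainly costs precision

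*Protocol*

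**What the plan says.** The protocol's Data Analysis section c sets one analytic sequence for Cohorts 1-5. A crude comparison comes first. Then: "Next we will conduct an analysis for each outcome accounting only for clustering", by "generalized estimating equations (GEE) with an unstructured correlation matrix and clustering by treatment site". Relative risks are to be obtained "using a log link function and a binomial distribution". A covariate-adjusted version of the same model may follow, then stratified analyses. No other correlation structure is named as a fallback.

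On design, the section on evaluation of effectiveness states: "We will use a matched cluster randomized design to evaluate the impact of each of the selected interventions". The site selection section adds: "In each pair, one clinic will randomly be assigned to receive early implementation of the minimum package of interventions". The sample size section assumes "24 clusters evenly split (randomized) between intervention and comparison groups". In the analysis section the pairs appear only in the descriptive step: "We will also look for differences within the randomized matched pairs". No pair term enters the model.

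**The concern.** An unstructured working correlation suits a few ordered repeated measurements, such as the same three visits in every patient. Here the cluster is a clinic and its members are different patients, each with one binary value per outcome. The matrix would give every pair of patient positions its own correlation. Patients are enrolled consecutively from records (Data Entry and Storage), so the third and seventeenth patient in one clinic have no counterpart in another. The parameters have no meaning and far outnumber the clinics.

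This is a stated choice. It governs the only analysis of the primary outcomes that allows for clustering, and the adjusted step reuses the same model. If it fails, a new structure has to be chosen once the data are in hand. If the software still prints a result, its standard error may be badly wrong.

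The lesser question is whether an analysis that ignores the randomised pairs gives up precision that the design paid for.

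**Working it through.** **Inputs.** Clusters: 24, 12 per arm. Coefficient of variation k = 0.1 and alpha 0.05 (sample size section; two-sided assumed). Patients per clinic m: 30 (Objective 1), 24 (Objectives 2, 3 and 5), 42 (Objective 4). Comparison-arm rates from Table 4: 60%, 80%, 80%, 52% and 30% for Objectives 1 to 5. The share s of between-clinic variance explained by pair is not given, so it is varied.

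**The plan's own figures.** 24 × 30 = 720, 24 × 24 = 576 and 24 × 42 = 1008 agree with Table 4. The Objective 1 cluster size itself could not be reproduced. The usual formula for a cluster trial with a coefficient of variation gives 19.2 per clinic unmatched or 22.0 matched. With 20% added these become 19.2 × 1.2 = 23.0 and 22.0 × 1.2 = 26.4, against 30 stated. The stated size is the larger, so this does not drive the point.

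**Step 1: parameter count.** Correlations = m(m−1)/2.
- m = 24: 24 × 23 / 2 = 276
- m = 30: 30 × 29 / 2 = 435
- m = 42: 42 × 41 / 2 = 861

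An average of products over 24 clinics has rank at most 24. An invertible 30 × 30 or 42 × 42 matrix needs more, before any patching by the software. An exchangeable structure needs one parameter.

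**Step 2: simulated fits** (log-binomial GEE, no true effect, k = 0.1, equal clinic sizes, one package).

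| Setting | Unstructured: converged | Unstructured: median robust SE | Exchangeable: converged | Exchangeable: median SE / empirical SD |
|---|---|---|---|---|
| Objective 1 (30, 60%) | 0 of 25 | 0.006 | 200 of 200 | 0.070 / 0.075 |
| Objective 2 (24, 80%) | 8 of 25 | 0.031 | 200 of 200 | 0.055 / 0.058 |
| Objective 4 (42, 52%) | 0 of 25 | 0.002 | 200 of 200 | 0.069 / 0.075 |

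Larger batches agree: 0 of 120 converged for Objective 1 and 13 of 120 for Objective 2. In a separate set of 96 trials the estimated matrix was singular every time. The Objective 2 standard error was erratic: another small batch gave a median of 0.223 with diverging estimates. The claim of far-too-small standard errors is therefore confined to Objectives 1 and 4.

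The exchangeable standard errors are slightly small: 0.070/0.075 = 0.93, 0.055/0.058 = 0.95, 0.069/0.075 = 0.92. This is expected with 12 clinics per arm. An uncorrected z test that ignores pairs rejected in about 7% of null trials when pairing explained nothing.

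**Step 3: leaving out the pairs.** Ratio of reported to true SE = √{[k²p² + p(1−p)/m] / [(1−s)k²p² + p(1−p)/m]}.

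Objective 1: k²p² = 0.01 × 0.36 = 0.0036 and p(1−p)/m = 0.24/30 = 0.0080.
- s = 0.50: √(0.0116/0.0098) = 1.09
- s = 0.75: √(0.0116/0.0089) = 1.14

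The same formula gives 1.09 to 1.14 for Objective 4. For Objectives 2 and 3 (0.0064 and 0.16/24 = 0.0067) it gives 1.15 to 1.26. For Objective 5 (0.0009 and 0.21/24 = 0.0088) it gives 1.02 to 1.04.

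**Step 4: ways to use the pairs.** Eleven pair dummies in the exchangeable log-binomial GEE, with Mancl-DeRouen standard errors, converged in 2 of 100 trials at 80% against 95%. At 60% the standard errors were about 36% too wide. Power for Objective 1 was about 50%, against 87% without pair terms. A paired t-test on the 12 within-pair log ratios of clinic proportions (11 df) held type I error near 5%. If pairing is uninformative, its power is about 81% for Objective 1 at 30/1.2 = 25 analysable patients per clinic. For Objectives 2 and 3 it is about 79% at 24 and 76% at 24/1.2 = 20.

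**The case against.** **GEE tolerates a wrong working correlation.** With a robust variance this holds when clusters are many and correlation parameters few. Here the parameters outnumber the clusters by more than ten to one, so it gives no protection.

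**Failure would be noticed.** This largely stands. A reader might infer that standard errors of 0.006 would be published, or that the trial has a false-positive rate near 90%. Rejection rates of that order did appear in simulation, but mostly in fits that had not converged. The protocol names SAS, STATA or SPSS, none of which was tested. The likelier harm is an unplanned change of structure.

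**An analysis plan may settle the details.** This stands for the variance estimator and reference distribution, on which the protocol is silent; the correction below is advice and not a charge of error. It does not excuse the correlation structure, which the protocol fixes. Nor does the protocol label this model primary, but no other analysis of these outcomes allows for clustering.

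**Ignoring the pairs is defensible.** This stands in large part. A reader might infer that omitting pairs stops the model fitting or inflates false positives. It does not stop the fit, and it mostly makes intervals too wide. An excess of 39% for Objective 1 needs k = 0.2, twice the protocol's value, and s = 0.75.

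**Covariates chosen on imbalance.** A reader might also fault the rule "should any imbalances between treatment groups be detected, we will adjust for those covariates in our GEE model". That step follows the crude and clustering-only estimates and replaces neither, and a fixed covariate list is commonly left to the analysis plan. It forms no part of this point.

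**Conclusion.** The point holds for the correlation structure. An unstructured matrix over 24, 30 or 42 unordered patients cannot be estimated from 24 clinics, and this affects every primary outcome of Objectives 1-5. The parameter count and the lack of a common patient order follow from the protocol alone. The convergence rates and standard errors rest on simulation with equal clinic sizes, k = 0.1 and one package.

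Omitting the pairs is secondary. It is a loss of precision, and its size depends on a pair share that the protocol does not give. With 50-75% assumed, standard errors are about 9-14% too wide for Objectives 1 and 4, more for Objectives 2 and 3, and little for Objective 5. If matching explains nothing, nothing is lost.

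**What to change.** In Data Analysis section c, replace unstructured by exchangeable. State a small-sample-corrected standard error (for example Kauermann-Carroll) with a t reference on 22 df, since there are 12 clinics per arm. This changes wording only and needs no more patients.

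To use the pairs and keep the relative risk, add a paired t-test on the 12 within-pair log ratios of clinic proportions (11 df), and say in advance which of the two analyses carries the conclusion. A paired test on plain differences in proportions would answer a different question, the risk difference. Do not add 11 pair dummies to the log-binomial GEE, for the reasons in step 4.

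The cost of the paired test is a few points of power if the matching proves uninformative. Objective 1 would have about 81%, but Objectives 2 and 3 would fall just below the planned 80% (about 79% at 24 per clinic, 76% at 20).

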## **c. Objectives**

The overall aims of this study are to assess the impact of a subset of the National Adherence Guidelines’ minimum package of interventions on HIV patients’ treatment outcomes at public sector clinics; estimate the costs of the interventions; and describe the cascade of care for TB, hypertension, and diabetes at these same clinics. All implementation of the interventions and generation of data will be done by NDOH; this protocol, which has been developed in partnership with the National Department of Health, is solely for the analysis of routinely collected data.

The specific objectives of the evaluation are to:

*Objective 1: Among HIV-infected patients newly eligible for antiretroviral therapy,* ***evaluate the impact of Fast Track Treatment Initiation Counselling on initiation and viral suppression****.*

Research questions:

- What is the effect of Fast Track Initiation Counselling on rates of initiating ART within 30 days of determining ART eligibility?
- What is the effect of Fast Track Initiation Counselling on rates of being alive, in care, and virally suppressed within 9 months of determining ART eligibility?

*Objective 2: Among HIV-infected patients who are stable on antiretroviral therapy,* ***evaluate the impact of Adherence Clubs on ART adherence and viral suppression****.*

Research questions:

- What is the effect of Adherence Clubs on medication possession over the first 3 months of intervention eligibility compared to standard of care?
- What is the effect of Adherence Clubs on rates of viral suppression within 12 months of intervention eligibility compared to standard of care?

*Objective 3: Among HIV-infected patients who are stable on antiretroviral therapy,* ***evaluate the impact of Decentralized Medication Delivery on ART adherence and viral suppression****.*

Research questions:

- What is the effect of Decentralized Medication Delivery on medication possession in the first 3 months after intervention eligibility compared to standard of care?
- What is the effect of Decentralized Medication Delivery on rates of viral suppression within 12 months of intervention eligibility compared to standard of care?

*Objective 4: Among HIV-infected patients who have poor adherence to antiretroviral therapy,* ***evaluate the impact of Enhanced Adherence Counselling on treatment adherence and viral suppression****.*

Research question:

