Each of the interventions, while implemented as a package of services, will be delivered to a unique population within each clinic: patients newly eligible for ART, patients stable on ART, patients with poor adherence, and patients lost from care. (The exception to this is patients who are stable on ART and could be provided with either decentralized medication delivery or adherence clubs, but not both.) This will allow us to estimate the effect of each intervention individually, in the context of implementation of the overall minimum package. During the early stages of implementation of the Adherence Guidelines it is possible that eligible patients at intervention sites might not all be enrolled in an intervention they are eligible for. In order to ensure that this evaluation does not by chance exclude eligible patients who are exposed to the interventions, enrolment at intervention sites will include not only those eligible for the intervention but also eligible patients who receive the intervention.

The following five interventions will be evaluated under this protocol. Each is described in detail in the National Adherence Guidelines[11]. (Note: Additional details about primary and secondary outcomes, eligibility criteria, sample size, and data sources are included in later sections of this protocol.)

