## **b. Inclusion and Exclusion Criteria**

For Objectives 1-5 and Objective 8, we will enroll a specific cohort of patients. These will be numbered in accordance with the objective number for Objectives 1-5; for Objective 8, the cohort will be called the “TBHD cohort”, in reference to tuberculosis, hypertension, and diabetes. This TBHD cohort will be made up of patients who have been screened for TBHD (50%) and patients who are newly diagnosed with TB, hypertension or diabetes (50%). For all cohorts, inclusion and exclusion criteria are as shown below. For Objectives 1-5, these criteria follow the December 2014 national guidelines for HIV care and ART[10] and November 2015 National Adherence Guidelines for Chronic Disease (HIV, TB and NCDs) [11].

*Cohorts 1-5 and TBHD cohort inclusion criteria*

- ≥ 18 years old
- Meet the inclusion criteria for one or more of Cohorts 1-8

*Cohorts 1-5 and TBHD cohort exclusion criteria*

- Not resident in the facility’s catchment area
- Recorded intention to transfer care to a different facility within 12 months
- Pregnant and eligible for PMTCT

*Objective 1/Cohort 1 inclusion criteria (Patients newly eligible for ART—fast track treatment initiation)*

- Determined to be eligible to start ART under prevailing national guidelines (CD4 count < 500, WHO Stage 3 or 4 condition, TB, cryptococcal meningitis)

*Objectives 2 and 3/Cohorts 2 and 3 inclusion criteria (Patients stable on ART—adherence clubs or decentralized medication delivery)*

- On same ART treatment regimen for at least 12 months
- Most recent viral load taken in past 6 months
- Two consecutive viral loads undetectable (<400 copies/ml^3^)

*Objective 4/Cohort 4 inclusion criteria (Patients on ART with poor adherence—enhanced adherence counseling)*

- On first line ART for at least 6 months
- Poor adherence as indicated by an elevated viral load (>400 copies/ml^3^)

*Objective 5/Cohort 5 inclusion criteria (Patients lost from ART programs—early patient tracing)*

- Initiated ART
- Fail to return for a scheduled appointment within 5 to 90 days from their appointment date

*Objective 8/TBHD cohort inclusion criteria (Tuberculosis, hypertension, and diabetes patients)*

- Screened for or diagnosed with for TB or hypertension within the last month, or diabetes within last 6 months

*Objective 8/TBHD cohort exclusion criteria (Tuberculosis, hypertension, and diabetes patients)*

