**Table 3. Evaluation outcomes**

| **Objective** | **Primary Outcome** | **Secondary outcomes** |
| --- | --- | --- |
| Fast track ART initiation counseling (Objective 1) | Proportion of patients who initiate ART within 30 days of becoming ART eligible (S) and the proportion of patients who are alive, in care, and virally suppressed (< 400 copies/ml^3^) within nine months of ART eligibility (L). | Proportion of patients who initiate ART within one week of becoming ART eligible  Demographic and clinical characteristics of patients who do and do not achieve primary outcomes (age, sex, baseline CD4 counts, TB diagnosis, other characteristics as allowed by data). |
| Adherence clubs (Objective 2) | Proportion of patients eligible for participation in an adherence club who receive all medications within the first four months after club eligibility (S) and the proportion virally suppressed (< 400 copies/ml^3^) at twelve months after club eligibility (L). | Proportion of patients consistently participating in club  Demographic and clinical characteristics of patients who do and do not achieve primary outcomes. |
| Decentralized medication delivery (Objective 3) | Proportion of patients eligible for decentralized medication delivery who receive all medications within the first three (S) months after delivery eligibility and viral suppression (< 400 copies/ml^3^) twelve months after delivery eligibility (L). | Proportion of patients consistently receiving medications  Demographic and clinical characteristics of patients who do and do not achieve primary outcomes. |
| Enhanced adherence counseling (Objective 4) | Proportion of patients with an elevated viral load who are alive, retained in care and resuppress their viral load (< 400copies/ml^3^) within three (S) and twelve months (L) of eligibility for enhanced adherence counseling. | Demographic and clinical characteristics of patients who do and do not achieve primary outcomes. |
| Early tracing of patients lost to follow up (Objective 5) | Proportion of patients eligible for early patient tracing who return to care within three (S) and twelve (L) months of eligibility. | Proportion of patients reached by tracers  Number of tracing attempts required; proportion of patients retained in care for at least one additional routine visit after tracing  Demographic and clinical characteristics of patients who do and do not achieve primary outcomes. |

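### Adherence clubs and decentralised delivery draw on one eligible pool with no rule for placing patients, so the randomisation does not identify their separate effects as section 10c says

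*Protocol*

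**What the plan says.** Section 4 presents the evaluation of every intervention as randomised: "We will use a matched cluster randomized design to evaluate the impact of each of the selected interventions". Section 8a shows what is actually allocated. Within each matched pair, "one clinic will randomly be assigned to receive early implementation of the minimum package of interventions", and the other clinic continues standard of care.

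Section 8b gives one list of criteria for both stable-patient cohorts, under the line "Objectives 2 and 3/Cohorts 2 and 3 inclusion criteria (Patients stable on ART—adherence clubs or decentralized medication delivery". Sections 4b and 4c repeat the same eligibility text for each. Section 3b calls these options substitutes, and section 4 says that stable patients "could be provided with either decentralized medication delivery or adherence clubs, but not both". Section 10c acknowledges this exception but still concludes that "we can estimate the impact of each intervention separately, as only one of them will be delivered to each cohort within a clinic"; the sentence goes on to limit this to a given moment.

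On enrolment, section 9d says only that patients are taken consecutively until targets are met. Section 4 adds, for intervention sites alone, that eligible patients who receive an intervention are also brought in. Sections 4b and 4c each ask for 24 patients per cluster.

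For the club short-term outcome, Objective 2 in section 3c asks about "medication possession over the first 3 months of intervention eligibility". Table 3 instead counts patients who "receive all medications within the first four months after club eligibility (S", the S marking the short-term outcome, and section 4b agrees with Table 3. The 80% planning rate for clubs in Table 4 is a three-month figure. Decentralised delivery uses three months throughout.

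**The concern.** A cluster-randomised comparison of clubs with standard of care needs a group of club patients at intervention clinics and the same kind of group at comparison clinics, formed by the same rule. The protocol gives no such rule. A comparison clinic has one undivided pool of stable patients from which it must fill both a club cohort and a delivery cohort. The reason in section 10c, that no one gets both at once, rules out overlapping exposure. It says nothing about how the two groups are formed.

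At stake is what the health department may conclude for Objectives 2 and 3. It plans to use the results to improve, target and budget the rollout, and Objective 7 attaches a cost per outcome to each intervention. Two results presented as separate randomised effects could be the same contrast reported twice, or could carry selection that the randomisation does not remove. The unequal outcome windows make the two results harder still to read side by side.

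**Working it through.** **1. The plan's own cohort sizes.** Inputs: 24 clinics, 24 patients per clinic per cohort (sections 4b, 4c and Table 4). 24 × 24 = 576 per cohort, as stated. Two cohorts give 1,152, or 48 per clinic. This is a maximum, because section 8b lets a patient meet the criteria for more than one cohort.

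Side check on power. Inputs: 80% against 95% (the 15% difference read as points, upwards), 12 clusters per arm, coefficient of variation 0.1, two-sided 0.05 (sidedness assumed).
- Variance term: v = [0.80×0.20 + 0.95×0.05]/24 + 0.1²×(0.80² + 0.95²) = 0.00865 + 0.01543 = 0.02407.
- Unmatched: √(11×0.15²/0.02407) − 1.96 = 1.25, power 0.89.
- Matched: √(10×0.15²/0.02407) − 1.96 = 1.10, power 0.86.

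The size of each cohort is therefore not the problem.

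**2. Could each clinic offer only one option?** Section 10c might be read that way. But both cohorts need 24 patients in all 24 clinics, which rules it out. Even if it were so, which clinic offered which option would not be randomised.

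**3. Cohorts formed by eligibility.** At package clinics, let shares a, b and c of stable patients get clubs, delivery or neither, with success rates r_a, r_b and r_c. The expected rate in any sample of eligible patients is a·r_a + b·r_b + c·r_c. Cohorts 2 and 3 are two samples from that same pool, so this is the expected rate in both. At comparison clinics both samples have the standard-of-care rate. Over a common window the two contrasts are equal in expectation. They are randomised, but neither is the effect of clubs alone or of delivery alone.

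**4. Cohorts formed partly by receipt.** Suppose there is no true effect, the pool rate is 80%, and stable patients split into club and delivery recipients. The recipients of one option make up share s and differ from the rest by gap d in underlying success. The comparison pool also contains patients of that type, so the bias is d × (1 − s), not d.

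| Share s | d = 5 points | d = 10 points |
| --- | --- | --- |
| 25% | 3.75 | 7.5 |
| 50% | 2.5 | 5.0 |
| 75% | 1.25 | 2.5 |

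At an even split, 2.5/15 = one sixth and 5/15 = one third of the target difference. The other option is biased the opposite way by d × s. The spurious relative risks are then 0.825/0.80 = 1.03 and 0.775/0.80 = 0.97 for d = 5, and 0.85/0.80 = 1.06 and 0.75/0.80 = 0.94 for d = 10. Both d and s are assumptions; the protocol gives neither.

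**5. The windows.** Club short-term outcome: 3 months in section 3c and in the Table 4 planning rate, 4 months in section 4b and Table 3. As a rough guide only, a constant and independent monthly rate would turn 80% over 3 months into 0.80^(4/3) = 0.743, about 74%, over 4. This would change the planning rate. It is not a bias between arms.

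**The case against.** The strongest reply is that the outcomes in sections 4b, 4c and Table 3 are defined among patients eligible for each option, not among those who received it, and that section 10c compares the arms by clinic. On that reading the comparison is protected by randomisation, and section 4 already says that effects are estimated in the context of the whole package. This stands in part. It is the better-supported reading, and it turns the defect into one of labelling. It does not rescue the claim of separate effects, because two samples of one pool still yield one contrast. The receipt sentence in section 4 also keeps the second reading open.

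A reader might go further and infer that patients or staff choose between clubs and delivery, so that the comparisons are confounded. The protocol does not say who decides or how. Capacity, availability or sequence are equally possible, and the club procedures it refers to are not at hand. A reader might also take the whole 5 to 10 point gap as bias, but the undivided comparison pool contains the same types of patient, which reduces it.

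The randomised-design wording comes from section 4, not from the sentence in section 10c. No direct test of clubs against delivery is planned. The 74% figure is weak, since clubs supply medication every two to three months rather than monthly.

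A statistical analysis plan, not seen here, could refine the models. How patients enter each cohort, the separability claim and the primary outcome window are matters the protocol itself sets out.

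**Conclusion.** The point holds for Cohorts 2 and 3. The randomisation supports one comparison among stable patients, package against standard of care, and not two intervention-specific effects. Under enrolment by eligibility there is no confounding; the result is valid but would be reported twice under different names. Under enrolment partly by receipt there is selection after randomisation, of about 2.5 to 5 points for the assumed gap of 5 to 10 points and an even split.

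The documents do not show that the second situation applies, so confounding should be stated as a possibility and not as a fact. The protocol accepts the same logic in section 4e, where it says that the impact of spaced appointments could not be told apart from that of clubs or delivery if given to the same patients.

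The 3- against 4-month conflict is a separate, plain contradiction in a primary outcome and depends on none of these assumptions.

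**What to change.** 1. Enrol stable patients by one eligibility rule applied identically in both arms. Receipt of an option should not bring a patient into the randomised comparison. Pooling alone does not achieve this while the receipt route in section 4 applies at intervention sites only.
2. Report as the randomised result for Objectives 2 and 3 one pooled comparison by clinic allocation of all stable patients so enrolled (up to 1,152 if nobody is in both cohorts), with one medication window.
3. Keep the club and delivery estimates, label them non-randomised, and adjust them for baseline characteristics.
4. Qualify the separability claim in section 10c, and the matching statements in section 4, for these two interventions.
5. Reconcile the 3- and 4-month windows across section 3c, section 4b, Table 3 and Table 4.

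The cost is mainly protocol and analysis wording, using data already planned. If some patients have entered through receipt, their route of entry must be identified, and the pooled comparison may fall below 1,152. The real price is that two of the five effectiveness objectives carry a weaker inferential status for their intervention-specific results.
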